### Pregnancy

Spironolactone is considered contraindicated in pregnancy or a category C drug (ie, potential benefits may warrant use in pregnant women despite potential risks).^1 15^ The main concern is around possible feminisation of the male fetus in the third trimester of pregnancy.^1^ Women of childbearing potential at risk of pregnancy will be asked to use their usual hormonal or barrier method of contraception during the first 24 weeks of the study and for at least 4 weeks (approximately one menstrual cycle) afterwards. A pregnancy test will be conducted for all participants at their baseline visit and documented in their medical notes. At weeks 6 and 12, the study nurse/doctor will ask participants to confirm that they are still using contraception and have not changed their contraceptive method. Participants who become pregnant will be asked to inform their local site study team as soon as possible and will not be able to continue in the study.

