## Methods

### Study design and setting

The study is a phase III, multicentre, double-blind, randomised superiority study, to investigate clinical and cost-effectiveness of spironolactone in the treatment of moderate or severe persistent facial acne in adult women compared with placebo, in addition to standard topical treatment. The design is pragmatic in order to have strong external validity and to inform real-world decision making for women with acne and their health professionals. Pragmatic design includes broad eligibility and recruitment strategies, a primary outcome that is relevant to participants, low intensity follow-up and an intention-to-treat (ITT) analysis. ‘Moderate to severe acne’, in the context of this study, is defined as acne that warrants treatment with oral antibiotics, as judged by the potential participant and study clinician.

Baseline and follow-up appointments are carried out by UK hospital dermatology centres in order to facilitate blood tests at baseline and clinical assessments. Participants continue on the allocated treatment (spironolactone or placebo) in combination with their usual topical treatment (if desired) for a total duration of 24 weeks with assessments at weeks 6 and 12. Primary outcome is assessed at week 12 with the patient-reported Acne-specific Quality of Life (Acne-QoL).^21 22^ From week 12, participants in both groups may receive ‘usual care’ from their usual clinical team, including oral treatments (oral antibiotics and hormonal treatments), and from week 24, participants may receive isotretinoin, if the participant and study clinician feel the need for rescue treatment. Trial participants receive shopping vouchers at baseline, 6 and 12 weeks (total £40). At week 24, participants stop taking their study treatment, are informed of their treatment group allocation and enter an unblinded observational follow-up period for up to 6 months (up to week 52 after baseline). During this observational final follow-up period, participants can ask their general practitioner (GP) to be prescribed spironolactone for their acne if they wish or pursue other acne treatments as part of usual care. Figure 1 illustrates the patient pathway through the study with table 1 summarising the study procedures.

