### Recruitment

Potential participants, identified in primary and secondary care, direct advertising in areas close to recruiting hospitals and social media advertising, are directed to the study website (https://www.southampton.ac.uk/safa) or to contact the local study team directly.

In primary care, recruitment is supported by general practices acting as participant identification centres local to the recruiting centres identifying potential participants either opportunistically or via database search based on an acne diagnosis and relevant prescription within the past 6 months and mail-out of invitation pack. In secondary care, potential participants are identified opportunistically in outpatient clinics and through screening new referral letters.

We use targeted social media advertising to promote the study, build study awareness and interest.

Participants are free to withdraw consent from the study at any time without providing a reason. They may withdraw from study treatment but remain in follow-up; withdraw from study and follow-up, but give permission for their data to be used in analyses; or completely withdraw from the study and not permit their data to be used.

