### Statistical methods

The study will be reported in accordance with Consolidated Standards of Reporting Trials (CONSORT) guidelines. A detailed statistical analysis plan (SAP) will be written and reviewed prior to the study database being locked.

The modified ITT population consists of all participants who have consented and have been randomised to a treatment arm and have complete data for the outcome being analysed. Analyses will be performed according to the modified ITT principle using a linear regression model. All analyses will be carried out in the modified ITT population, with the level of missing data reported, unless otherwise stated. The frequency and pattern of missing data will be examined and a multiple imputation model will be used as a sensitivity analysis if appropriate.

For the primary analyses, descriptive statistics will be obtained for the randomised groups to characterise recruited participants and assess baseline comparability. For the primary outcome, a linear regression model will be used to analyse Acne-QoL symptom subscale at week 12, adjusting for baseline variables (including baseline Acne-QoL symptom subscale score, use of topical treatments, use of hormonal contraception/ethinylestradiol/cyproterone acetate (co-cyprindiol) and randomisation stratification variables (centre, baseline severity (IGA <3 vs 3 or more)). A full list of covariates and model specification will be set out in the SAP. A 95% CI for the least squares mean difference between arms in Acne-QoL symptom subscale at week 12 will be calculated.

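### Pregnancy is written as an exit from the whole study, so later questionnaire outcomes of randomised women are lost when they need not be

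*Protocol article*

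**What the plan says.** All places are in the protocol article.

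- **Pregnancy.** A participant who becomes pregnant is asked to tell her site promptly and "will not be able to continue in the study". The sentence does not separate study treatment from follow-up and sets no time limit. Contraception is requested "during the first 24 weeks of the study and for at least 4 weeks (approximately one menstrual cycle) afterwards".
- **Study design and setting.** The pragmatic features include "low intensity follow-up and an intention-to-treat (ITT) analysis". Study treatment stops at week 24, and observation continues for up to 52 weeks from baseline.
- **Recruitment.** "Participants are free to withdraw consent from the study at any time without providing a reason". Three levels of withdrawal follow, of which the first is: "They may withdraw from study treatment but remain in follow-up".
- **Statistical methods.** The modified ITT population is limited to randomised participants who "have complete data for the outcome being analysed". For missing data, "a multiple imputation model will be used as a sensitivity analysis if appropriate".
- **Tables 1 and 2.** Acne-QoL, the Participant's Global Assessment, self-assessed improvement and EQ-5D-5L are completed by the participant. Of the clinical effectiveness outcomes in Table 2, only the IGA is graded by a clinician, at weeks 6 and 12. The text after Table 1 allows remote visits at those weeks and posting of questionnaires.

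**The concern.** Under intention to treat, a randomised woman's outcome is wanted whether or not she stays on the tablets. The article otherwise follows this: after week 12 participants may start other oral acne treatments, and after week 24 isotretinoin, and they are still assessed. Pregnancy is the one post-randomisation event for which the article itself prescribes an exit from the study.

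Combined with an analysis set that needs an observed outcome, the exit becomes an exclusion from analysis after randomisation. At stake are a few avoidable missing outcomes at weeks 12, 24 and up to 52, and a gap between the declared principle and what happens to these women.

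**Working it through.** **1. Reading the sections together.** A woman who leaves before week 12 has no week-12 Acne-QoL symptom score. She fails the complete-data condition and is not in the primary analysis. A woman who leaves later keeps the outcomes already collected and loses the rest. Imputation would bring such women back only in a sensitivity analysis, and only if that analysis is judged appropriate.

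**2. The period after treatment.** Treatment ends at week 24. Contraception is requested until at least 24 + 4 = 28 weeks, and the exclusion criterion covers only women intending pregnancy within 6 months. A woman who conceives after week 28 is off study treatment and within the rules, yet the sentence as written still removes her before the final questionnaire. Stopping study treatment cannot be the reason for that exit.

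**3. The plan's sample size.** Inputs from the Sample size section: power 90%, alpha 0.05 (taken as two-sided), effect size 0.35, 20% loss, correlation with baseline 0.293.
- A two-sample t-test at effect size 0.35 gives 172.5, so 173 per group, or 346.
- With 20% loss: 173 / 0.8 = 216.25, so 217 per group, or 434.
- Deflation factor: 1 − 0.293² = 0.914. Then 173 × 0.914 = 158.2, so 159; 159 / 0.8 = 198.75, so 199 per group, or 398.

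All three stated totals reproduce.

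**4. Number affected.** The article gives no pregnancy rate, so 1% to 3% over 24 weeks is an assumption.
- 398 × 0.01 = 4.0 and 398 × 0.03 = 11.9, so about 4 to 12 women.
- If the risk is even over time, half of these fall before week 12: about 2 to 6.
- Pregnancies after week 24 would add losses at the final questionnaire only. The article offers nothing by which to size them.

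**5. Power for the primary comparison.** If these exits fall within the 20% allowance, nothing changes. If they come on top, the evaluable number is 398 × (0.80 − p), where p is the proportion leaving. The adjusted SD is 5.8 × √0.914 = 5.55, the difference is 2 points, and power is by the normal approximation.

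| p | Women leaving | Evaluable | Power |
|---|---|---|---|
| 0 | 0 | 318.4 | 89.6% |
| 0.5% | 2 | 316.4 | 89.4% |
| 1% | 4 | 314.4 | 89.2% |
| 2% | 8 | 310.4 | 88.8% |
| 3% | 12 | 306.5 | 88.4% |

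Even if all of the assumed 3% left before week 12, the cost is 89.6 − 88.4 = 1.2 percentage points.

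**6. Possible bias.** Suppose exits occur in one arm only, at proportion q, and those women's scores would have differed from the rest of the arm by D points. The arm mean then moves by about q × D. With q = 2% and D = 5.8 (one SD), the shift is 0.02 × 5.8 = 0.12 points; with D = 10 it is 0.20. The target difference is 2 points.

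**The case against.** The strongest reply is that the sentence is condensed wording. It closes a paragraph about contraindication and contraception, and may only mean that study treatment ends. That is possible, but the article does not say so, and elsewhere it does distinguish leaving treatment from leaving follow-up. If that is the meaning, the wording still needs correcting.

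A second reply is that the operative analysis is modified ITT, so a pregnant participant is handled like anyone with a missing outcome and her earlier data stay in. This is correct, and the wider tension between ITT and a complete-data population exists without the pregnancy rule. But the rule creates missing outcomes that could have been collected.

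Third, whether outcomes observed during pregnancy are wanted is partly a choice of estimand. That stands as a cost of the change, although the ITT principle the article declares points towards keeping them.

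Two stronger readings are tempting and are not supported:
- *The Pregnancy and Recruitment sections contradict each other.* They do not govern the same event. Recruitment lists what a participant may choose; Pregnancy imposes an exit. Recruitment shows only that being off treatment and in follow-up is already a recognised status.
- *Safety or pregnancy-outcome data collection stops.* The article does not show this. The pregnancy is to be reported to the site. Oversight and monitoring lets serious events be reported at any time and asks GPs to notify them. Table 1 schedules a week-12 reminder to report related adverse events up to 52 weeks. Follow-up of exposed pregnancies is a detail that an article may leave to the full protocol.

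**Conclusion.** The point holds as a minor one. Taken literally, the pregnancy rule ends outcome follow-up for randomised women, including after study treatment is over, and the complete-data rule then removes them from all later analyses. The loss is imposed by the protocol and fits poorly with the stated ITT principle.

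A reader might infer that the primary result is at risk, but the figures do not support that. The count rests on an assumed pregnancy rate, and the contraception request, the checks at weeks 6 and 12 and the eligibility criteria should all hold it down. The sample size needs no change. The case for acting is consistency and fewer missing outcomes at negligible cost.

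**What to change.** Leave the rule on study treatment in pregnancy as it stands. Reconcile Study design and setting, Recruitment, Pregnancy and Statistical methods by adding one statement: participants who become pregnant remain in follow-up for participant-reported outcomes on the planned schedule unless they withdraw consent, and are analysed in their randomised group. If the existing sentence was only ever meant to govern study treatment, it should say so.

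The cost is one sentence in the protocol, matching participant information and a few extra questionnaires. The downside is that a few scores will reflect pregnancy and stopped treatment. A count of such participants by arm at each time point would let readers judge this.

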### Sample size

Based on comparison of the Acne-QoL symptom score between groups at week 12, power 90%, alpha 0.05 and seeking a difference between groups of 2 points on the symptom subscale (SD 5.8, effect size 0.35), 346 participants are needed. Allowing for 20% loss to follow-up gives a total 434 participants (217 per group). Following discussions with oversight committees postfunding award, the sample size was recalculated. Allowing for a correlation with baseline of 0.293 and a deflation factor of 1-ρ2^27^ gives a total sample size required of 398 participants. A difference of 2 points on the symptom subscale and an SD of 5.8 (equivalent to an effect size 0.35) is in line with that reported in studies in a similar patient group and with the MCID reported for Acne-QoL.^21 22^

### Data collection methods

Participant data are entered into study electronic case report forms (eCRFs) via a remote data collection tool (Medidata Rave) by trained hospital research personnel with specific roles on the study and are regularly checked for missing or anomalous values by the Southampton Clinical Trials Unit (CTU) study staff.

### Data management

Participant data are pseudonymised by assigning each participant a participant identifier code, which is used to identify the participant during the study and for any participant-specific communication between Southampton CTU and recruiting sites. The site retains a participant identification code list which is only available to site staff and stored in a secure location at site.

### Patient and public involvement (PPI)

This study addresses a priority area identified as important to patients and health professionals by the James Lind Alliance Priority Setting Partnership for Acne.^7^ We gained feedback from a virtual acne-specific patient panel, convened through ‘People in Research’ (https://www.peopleinresearch.org). A patient survey was carried out with the support of the UK Dermatology Clinical Trials Network in order to inform the study design. Findings suggested that participants would find it difficult to abstain from using topical treatments for more than 12 weeks and that asking participants to take a placebo for 1 year would also be a barrier to recruitment.

Two public contributors with experience of acne attend all Trial Management Group (TMG) meetings to ensure that decisions around the study design are informed by their perspective; study procedures are feasible for participants, and study materials are readable and include all the relevant information that participants would want. Public contributors influenced the trial design and delivery, for instance, by advocating use of social media advertising to improve recruitment, arguing against repeated measures in this patient group and that an upper age limit of 50 years was arbitrary and could appear discriminatory.

### Statistical methods

The study will be reported in accordance with Consolidated Standards of Reporting Trials (CONSORT) guidelines. A detailed statistical analysis plan (SAP) will be written and reviewed prior to the study database being locked.

The modified ITT population consists of all participants who have consented and have been randomised to a treatment arm and have complete data for the outcome being analysed. Analyses will be performed according to the modified ITT principle using a linear regression model. All analyses will be carried out in the modified ITT population, with the level of missing data reported, unless otherwise stated. The frequency and pattern of missing data will be examined and a multiple imputation model will be used as a sensitivity analysis if appropriate.

For the primary analyses, descriptive statistics will be obtained for the randomised groups to characterise recruited participants and assess baseline comparability. For the primary outcome, a linear regression model will be used to analyse Acne-QoL symptom subscale at week 12, adjusting for baseline variables (including baseline Acne-QoL symptom subscale score, use of topical treatments, use of hormonal contraception/ethinylestradiol/cyproterone acetate (co-cyprindiol) and randomisation stratification variables (centre, baseline severity (IGA <3 vs 3 or more)). A full list of covariates and model specification will be set out in the SAP. A 95% CI for the least squares mean difference between arms in Acne-QoL symptom subscale at week 12 will be calculated.

### Health economics analysis

If the intervention is found effective, a within-study economic evaluation will be undertaken to assess value for money of spironolactone plus usual care versus placebo plus usual care. The main perspective of the analysis will be that of the NHS over the 24-week treatment period, although a secondary analysis will assess the importance of a broader perspective by incorporating out-of-pocket costs related to acne and any productivity/employment impacts for people with persistent acne.^28^

Costs, including intervention and wider NHS resource use, are being recorded in the study eCRF for the former, while wider NHS resource use is captured in participant questionnaires at baseline and weeks 6, 12 and 24.

Costs will be valued using published unit costs for a common recent price year to estimate mean cost per participant in each arm.^29–31^

Review of the reliability, validity and responsiveness of three generic preference-based measures (EQ-5D, Short-Form Six Dimensions (SF-6D) and Health Utilities Index (HUI)) in skin conditions only found evidence to support the use of the EQ-5D in skin diseases with no studies looking at measurement properties for the SF-6D or HUI in skin disease.^32^ Problems on the EQ-5D domains were found to be substantially higher in the acne sample receiving specialist care than in an age-truncated population sample (aged 20–39 years) particularly on the pain/discomfort (42.1% in the acne sample vs 17.7% in an age-truncated population sample) and anxiety/depression domains (52.8% vs 12.5%, respectively).^33^ EQ-5D was found to be responsive to change, with moderate effect sizes at 4 and 12 months (−0.44 and −0.53, respectively).^33^ We will value the EQ-5D-5L in our primary analysis in line with NICE recommendations at the time of analysis.^3 34^ Quality-adjusted life years (estimated using EQ-5D-5L^32 33^) for the study period will be estimated using linear interpolation and area under the curve with and without baseline adjustment.^35^ Clinical measures were found to be more responsive to change than the generic measures (shown by larger effect sizes), and combination of generic preference-based measures with the use of disease specific measure was concluded to be desirable.^33^ The primary economic evaluation will be an incremental cost utility analysis to enable the cost effectiveness to be compared across a range of health conditions and interventions such that decision makers can use the information to inform prioritisation of healthcare. A secondary cost effectiveness analysis using the disease-specific Acne-QoL will be presented as appropriate, though it should be noted that this instrument does not have utility weights available and it is unclear what incremental cost per unit of change on the Acne-QoL represents good value for money. All analyses will be conducted and presented using established methods.^28 36^

If spironolactone is not found to be clinically effective, a full economic evaluation will not be conducted. Instead, estimates of mean costs and utility per participant will be presented at the various study time points as these may be informative for other researchers undertaking future economic studies or economic modelling in this clinical area.

A detailed health economic analysis plan will be written prior to the study database being locked.

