## Abstract

**Introduction:**

Acne is one of the most common inflammatory skin diseases worldwide and can have significant psychosocial impact and cause permanent scarring. Spironolactone, a potassium-sparing diuretic, has antiandrogenic properties, potentially reducing sebum production and hyperkeratinisation in acne-prone follicles. Dermatologists have prescribed spironolactone for acne in women for over 30 years, but robust clinical study data are lacking. This study seeks to evaluate whether spironolactone is clinically effective and cost-effective in treating acne in women.

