**Methods and analysis:**

Women (≥18 years) with persistent facial acne requiring systemic therapy are randomised to receive one tablet per day of 50 mg spironolactone or a matched placebo until week 6, increasing to up to two tablets per day (total of 100 mg spironolactone or matched placebo) until week 24, along with usual topical therapy if desired. Study treatment stops at week 24; participants are informed of their treatment allocation and enter an unblinded observational follow-up period for up to 6 months (up to week 52 after baseline). Primary outcome is the Acne-specific Quality of Life (Acne-QoL) symptom subscale score at week 12. Secondary outcomes include Acne-QoL total and subscales; participant acne self-assessment recorded on a 6-point Likert scale at 6, 12, 24 weeks and up to 52 weeks; Investigator’s Global Assessment at weeks 6 and 12; cost and cost effectiveness are assessed over 24 weeks. Aiming to detect a group difference of 2 points on the Acne-QoL symptom subscale (SD 5.8, effect size 0.35), allowing for 20% loss to follow-up, gives a sample size of 398 participants.

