**Secondary outcome measures**				
Acne-QoL symptom subscale score	X	X	X	X
Acne-QoL other subscales	X	X	X	X
Acne-QoL total score*	X	X	X	X
Participant self-assessed overall improvement†	X	X	X	X
IGA‡	X	X		
Participant’s Global Assessment§	X	X	X	X
Participant satisfaction with study treatment¶			X	
Health-related quality of life using EQ-5D-5L**	X	X	X	X
Costs incurred	X	X	X	X
Cost-effectiveness††			X	

*Self-perception, role—emotional and role—social.

†Recorded on a 6-point Likert Scale with photographs taken at the baseline visit to aid recall.^37^

‡5-point scale ranging from clear to severe (0, clear; 1, almost clear; 2, mild; 3, moderate; 4, severe).^25^

§Same scale as the IGA but written in plain English for participants’ use.

¶Asked prior to revealing treatment allocation after 24 weeks.

**The EQ-5D-5 L assesses five dimensions: mobility, self-care, usual activities, pain/discomfort and anxiety/depression.

††Using EQ-5D-5L and data on health resource use during the study.

‡‡The follow-up questionnaire will be sent out 6 months or sooner after the 24-week time point.

IGA, Investigator’s Global Assessment.

The safety profile of spironolactone is well established.^15 16^ Consequently, we collect information about adverse reactions of special interest, both to inform the dose review decision from week 6 onwards as well as to learn more about incidence of side effects in this population. We also collect and report all serious adverse events (SAEs).

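### The full economic evaluation is run only if spironolactone is found effective, although cost-effectiveness is stated elsewhere as an unconditional aim and 24-week secondary outcome

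*Protocol article*

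**What the plan says.** The Health economics analysis section of the protocol article sets the condition twice. It opens with: "If the intervention is found effective, a within-study economic evaluation will be undertaken to assess value for money". Near its end it adds: "If spironolactone is not found to be clinically effective, a full economic evaluation will not be conducted". The next sentence gives the fallback: "Instead, estimates of mean costs and utility per participant will be presented at the various study time points". When the evaluation is run, "The primary economic evaluation will be an incremental cost utility analysis", with QALYs from the EQ-5D-5L, an NHS perspective and a 24-week horizon. The section does not say which outcome, time point or threshold decides effectiveness.

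Elsewhere cost-effectiveness carries no condition:

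- Abstract, Introduction: "This study seeks to evaluate whether spironolactone is clinically effective and cost-effective in treating acne in women".
- Abstract, Methods and analysis, in the sentence that lists the secondary outcomes: "cost and cost effectiveness are assessed over 24 weeks".
- Study design and setting: the trial is designed "to investigate clinical and cost-effectiveness of spironolactone in the treatment of moderate or severe persistent facial acne in adult women compared with placebo".
- Table 2, Secondary outcome measures: cost-effectiveness is marked at 24 weeks, with the footnote "Using EQ-5D-5L and data on health resource use during the study".

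**The concern.** The two parts of the article cannot both be followed after an unfavourable clinical result. The aims and Table 2 promise an answer on cost-effectiveness, and the Health economics analysis section withholds it.

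The condition is also a poor criterion for the question it controls. Cost-utility analysis estimates differences in cost and in QALYs together. Not finding a clinical effect is not evidence that there is none, and still less evidence that 24-week costs and EQ-5D-5L QALYs are the same in both arms. At stake is one stated objective: the incremental comparison and its uncertainty would be missing in exactly those cases where the clinical result is unclear and a decision maker most needs to see how uncertain the value for money is.

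**Working it through.** **Comparison of the condition with what it controls.** The article does not define the condition. If it is read as the primary outcome, it differs from the economic analysis in three ways:

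| | Primary clinical outcome | Primary economic analysis |
|---|---|---|
| Measure | Acne-QoL symptom subscale | EQ-5D-5L QALYs and NHS costs |
| Time | Week 12 | 24 weeks |
| Question | Difference in symptom score | Incremental cost and QALYs, jointly |

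Study design and setting also allows usual-care oral treatments in both arms from week 12. Costs and utilities can therefore diverge after the primary outcome has been measured.

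**What the fallback leaves out.** Mean costs and utilities by time point, if shown by arm, would let a reader form rough differences. They would not give the uncertainty of the QALY difference, which depends on correlation between a participant's repeated utilities. Nor would they give the joint uncertainty of cost and QALYs, or the baseline-adjusted QALY comparison that the section plans.

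**Reproducing the plan's own sample size.** The inputs come from the Sample size section: difference 2, SD 5.8, effect size 0.35, power 90%, alpha 0.05 (taken as two-sided, which is not stated), 20% loss and correlation 0.293. Allocation is 1:1.

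1. A t-test at effect size 0.35 needs 172.5 per arm, rounded up to 173, so 346 in total. This matches the stated 346.
2. 346 / 0.8 = 432.5, or 434 as an even total with 217 per arm. This matches.
3. Deflation factor: 1 − 0.293² = 0.9142. Then 217 × 0.9142 = 198.4, rounded up to 199 per arm, so 398. This matches.

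**Illustration of how often the full evaluation would be skipped.** Assumption: the condition is two-sided p<0.05 in favour of spironolactone on the week-12 primary outcome.

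- Number analysed: 398 × 0.8 ≈ 318, or about 159 per arm.
- Adjusted SD: 5.8 × √0.9142 = 5.55.
- SE of the difference: 5.55 × √(4/318) = 0.622.
- Probability of no full evaluation at true difference d: 1 − Φ(d/0.622 − 1.96).

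| True difference (points) | d/SE | Chance of no full evaluation |
|---|---|---|
| 2.0 | 3.22 | about 10% |
| 1.5 | 2.41 | about 33% |
| 1.25 | 2.01 | about 48% |
| 1.0 | 1.61 | about 64% |
| 0.5 | 0.80 | about 88% |

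**The case against.** Four points can fairly be made for the plan.

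1. **The condition is not defined, so it need not be the week-12 test.** A reader might infer that the evaluation hangs on the significance of the primary outcome. The article does not say so. Effectiveness could be judged on several outcomes, on week 24, or against the 2-point minimum clinically important difference. A health economic analysis plan is promised before database lock and may define it. This stands: the percentages above are an illustration, and the missing definition is not counted as a fault in itself. The rule that the evaluation is conditional is, however, fixed in the article.

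2. **Economic results are not suppressed.** A reader might infer that all economic reporting is cancelled after a null result, or that this is selective reporting. Neither is supported. Mean costs and utilities are still presented, and the rule was published in advance. What is lost is the incremental analysis and its uncertainty.

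3. **The size is modest at the design effect.** At 2.0 points, the 10% is simply the planned type II error. The figures of 33% and above apply to true differences below the article's own minimum clinically important difference. This stands too, but a smaller clinical effect does not settle the value-for-money question, which is why that question is analysed separately.

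4. **The consequences are contained.** The primary analysis, the sample size and data collection are unaffected, and the incremental analysis could be done later from the same data. This limits the seriousness but does not remove the contradiction.

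**Conclusion.** The point holds in a limited form. The article makes the full incremental evaluation conditional on a finding of effectiveness, while stating cost-effectiveness unconditionally in the abstract, the design statement and Table 2. Following it as written could leave a stated objective unanswered, on a criterion that does not determine 24-week incremental costs or QALYs. That conclusion needs no arithmetic and does not depend on how effectiveness is judged.

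The size does depend on it. On the assumed reading (two-sided p<0.05 in favour on the week-12 primary outcome, about 318 analysed, SD 5.8, correlation 0.293), the chance of no full evaluation runs from about 10% at 2.0 points to 64% at 1.0.

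Two further inferences are tempting but unsupported:

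- **Inflated QALY gains.** One might say that running the evaluation only after a significant result inflates the QALY gain. Under the same assumption, the mean symptom-score estimate given significance is 1.64 at a true 1.0 and 2.13 at a true 2.0. That inflation is in the Acne-QoL score. The documents give no correlation between that score and QALYs, so no bias in QALYs can be stated.
- **A cheap drug with a small effect.** One might say that such a drug could still be cost-effective. The documents give no price and no willingness-to-pay threshold, so this cannot be argued from them.

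The matter should be corrected, but it does not touch the primary clinical conclusion.

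**What to change.** Remove the two conditional sentences in Health economics analysis, together with the fallback that follows the second. State instead that the incremental cost-utility analysis over 24 weeks, with the joint uncertainty of costs and QALYs, will be done and reported whatever the clinical result. The way uncertainty is presented can be left to the health economic analysis plan.

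If the sponsor prefers to keep a condition, the less satisfactory alternative is to define it (outcome, time point and threshold) before unblinded data are seen, and to make the abstract, the design statement and Table 2 conditional to match. That removes the contradiction, but the objective could still go unanswered.

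The cost is a little more analyst time. The sample size does not change, and no extra data are needed: Table 1 schedules the EQ-5D-5L and the resource use questionnaire at baseline and weeks 6, 12 and 24 for all participants, whatever the result.
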